### Data collection

#### Patient assessment

The research nurse will use a laptop computer to collect demographic data from all consenting patients and to administer the GPGOG, CAMCOG, GDS, WHOQOL-BREF, GPAQ and ADL (for patients in CAMCOG dementia range only). Patients will be asked about any memory-related services accessed, referral to Alzheimer's Australia, and referral to a specialist for memory problems. The research nurse will compile a list of all prescription and over the counter medications currently used by the patient, so that medication can be excluded as a cause of cognitive impairment. Complementary and alternative medicines will be included. In addition the nurse will perform a "75 + Health Assessment" rebateable under the Australian Medicare system on eligible patients where this has been requested by the GP. These data will not be used by the study, but are returned to the GP for his or her use. This part of the assessment is a provided as a service to the GP. Brief questions used in our previous research will be used to measure the acceptability of the interview process. We will ask patients to send answers back in a reply-paid envelope, to avoid bias due to the presence of the nurse. At the completion of the assessment the nurse will hand the patient a sealed envelope. In the case of patients in the intervention group, it will direct the patient to obtain an appointment with his/her GP as soon as possible to follow up on the 75+ Health Assessment and to have the GPCOG re-administered. In the case of patients in the waitlist group, it will suggest a follow up for the 75 Plus Health Assessment only. Patients will be reassessed using the same instruments at 12 and 24 months after baseline interviews.

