### Sample size

It was calculated that 45 patients with dementia in each group (Waitlist and Intervention) would give a power of 0.9 to detect a 7% difference between the change in pre and post scores on any of the four domain scales of the WHOQOL-BREF with a type 1 error of .05. The population standard deviation used is 18.5 [32] and the Pearson correlation coefficient between the pre and post scores for both groups is assumed to be 0.7, based on pilot data available from the University of Melbourne.

The hierarchical nature of the study design will probably lead to some within cluster correlations and the greatest impact of this is likely to be associated with patients clustered within a GP practice. Clustering within each GP may be discounted, as it is anticipated that most GPs will have less than five patients with dementia in this study. Assuming an intra-class correlation coefficient of 0.05 and an average cluster size of 5 patients with dementia in a practice, this gives a design effect of 1.45 and a total sample size of 54 patients per group. We will therefore allow for 56 patients with dementia in the waitlist group and 112 in the intervention group to allow for comparison of outcomes between the waitlist and intervention groups overall. This sample size also allows comparison of "case finding" and "screening" patients and their support persons within the group. It is assumed that about 50% of participants will be screening and 50% case finding. Thus, we aim to recruit 168 participants with dementia overall. Based on a dementia prevalence of approximately 10% in over 75 year old Australians [37], we aim to recruit a total of 2,000 participants.

For the GDS, following the same set of assumptions and approach as for the WHO QOL-BREF (power, type 1 error and correlations), 45 patients in both the Intervention and Waitlist groups would allow detection of an average difference in the change in pre and post scores of 0.9 points on the 15 point GDS, using a standard deviation of 2.39 [28]. The cluster effect would be the same as for the WHOQOL-BREF.

For an estimate of test re-test reliability on the GPCOG a sample size of 100 will be used to ensure the correlation is estimated to a reasonable precision. The 95% confidence interval for a Pearson correlation of 0.9 would be [0.86, 0.93] and for a correlation of 0.80 [0.73, 0.85].

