#### Test parameters of the GPCOG

The GPCOG will be compared with the DSM diagnosis derived from the CAMCOG as a 'gold standard', and sensitivity, specificity, positive predictive value, negative predictive value and misclassification rate will be calculated. ROC curve analysis will be employed to examine the discrimination ability of the GPCOG test (i.e. ability to detect dementia) relative to MMSE. This is important as the MMSE is now commonly used in General Practice. GPCOG test-re-test and inter-rater reliability (between the nurse and the GP) will be calculated, using the kappa coefficient and intra-class correlation coefficient.

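### The precision stated for n = 100 in the GPCOG test-retest study is not the 95% precision of the ICC or kappa that will be reported (minor)

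*Protocol article*

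**What the plan says.** The last paragraph of *Sample size* in the protocol article sets the size of the GPCOG test-retest study: "a sample size of 100 will be used to ensure the correlation is estimated to a reasonable precision". Its only support is two intervals. The first reads "The 95% confidence interval for a Pearson correlation of 0.9 would be [0.86, 0.93", and the second, "for a correlation of 0.80 [0.73, 0.85".

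Under *Test parameters of the GPCOG* the analysis is described as follows: "GPCOG test-re-test and inter-rater reliability (between the nurse and the GP) will be calculated, using the kappa coefficient and intra-class correlation coefficient". Pearson's coefficient is not mentioned there. The section does not say whether kappa is weighted or at which GPCOG cut-off it is taken. No GPCOG-positive rate appears anywhere; the nearest figure is the dementia prevalence of about 10% used under *Sample size*.

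The figure of 100 is tied to test-retest only. For nurse-GP agreement, *Patient assessment* sends intervention patients to their GP "to follow up on the 75+ Health Assessment and to have the GPCOG re-administered", and no number of pairs is set.

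**The concern.** The article names one statistic when it justifies the sample size and two others when it describes the analysis. A precision statement is useful only if it describes the estimate that will be published. Two things could go wrong. The printed limits may not be right even for the statistic they name. They may also not carry over to the ICC or to kappa. Kappa is the more exposed of the two, because the variance of an unweighted two-category kappa depends on how many patients test positive and grows as positives become rare. A reader who takes the printed lower limit of 0.73 at 0.80 as a guide to what 100 retests will show could expect more of the kappa result than it can give.

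**Working it through.** **Inputs from the document.** n = 100; coefficients 0.90 and 0.80; printed limits 0.86 to 0.93 (width 0.07) and 0.73 to 0.85 (width 0.12), labelled 95%.

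**Inputs assumed.** Two GPCOG administrations per patient. For kappa: unweighted, two categories, the same positive rate p on both occasions, and p = 50%, 20% or 10%. The 10% borrows the plan's dementia prevalence as a proxy.

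**Step 1: the plan's own figures.** Fisher's z interval is tanh(atanh(r) ± z/√(n − 3)), with √97 = 9.849.

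| r | atanh(r) | 95% (± 1.960/9.849 = 0.199) | 90% (± 1.645/9.849 = 0.167) | Printed as 95% |
|---|---|---|---|---|
| 0.90 | 1.472 | 0.855 to 0.932 | 0.863 to 0.927 | 0.86 to 0.93 |
| 0.80 | 1.099 | 0.716 to 0.861 | 0.731 to 0.853 | 0.73 to 0.85 |

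The 90% limits round exactly to both printed pairs. The 95% limits do not. Replacing n − 3 by n − 1.5, n − 1 or n, or using an untransformed interval, does not give both pairs at 95% either. A 95% interval that rounds to both pairs needs n between 128 and 154. At 0.90 the gap is a matter of rounding (0.855 against a printed 0.86); at 0.80 it is plain. The true 95% widths are 0.077 and 0.145.

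**Step 2: the ICC.** With two ratings and the one-way form, F = (1 + ICC)/(1 − ICC). F is divided by the 97.5% point of F(99, 100), which is 1.484, for the lower limit, and multiplied by that of F(100, 99), which is 1.485, for the upper. Each is converted back by (F − 1)/(F + 1).

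- ICC 0.90: F = 19, limits 12.80 and 28.22, giving 0.855 to 0.932 (width 0.076).
- ICC 0.80: F = 9, limits 6.06 and 13.37, giving 0.717 to 0.861 (width 0.144).

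These are the true 95% Pearson intervals to within about 0.001.

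**Step 3: unweighted dichotomous kappa.** With equal margins, the Fleiss-Cohen-Everitt large-sample variance reduces to

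(1 − κ)/n × [(1 − κ)(1 − 2κ) + κ(2 − κ)/(2p(1 − p))].

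At κ = 0.80 and n = 100 this is 0.002 × [−0.12 + 0.96/(2p(1 − p))].

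| p | Bracket | SE | 95% interval | Width | Width / 0.145 |
|---|---|---|---|---|---|
| 50% | 1.80 | 0.060 | 0.68 to 0.92 | 0.235 | 1.6 |
| 20% | 2.88 | 0.076 | 0.65 to 0.95 | 0.298 | 2.1 |
| 10% | 5.21 | 0.102 | 0.60 to 1.00 | 0.400 | 2.8 |

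Simulation of 200,000 tables gave standard deviations of 0.060, 0.078 and 0.111, so the formula is accurate at 50% and slightly optimistic at 10%.

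**The case against.** The strongest reply is that sizing on one coefficient and reporting others is not a contradiction. The ICC behaves like Pearson, so one of the two planned statistics is adequately served by n = 100. This stands, and it rules out reading the sample size itself as wrong.

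Second, a reader might infer that the plan promises a given precision for kappa, or a reproducible classification, and then breaks that promise. It does not. The text speaks of the precision of the correlation, sets no target and gives no figure for kappa.

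Third, the loss for kappa is conditional. Nothing says kappa is unweighted or dichotomous, and a quadratically weighted kappa on the scores would behave much like the ICC. The 10% is dementia prevalence, not the rate of positive GPCOG results, and the make-up of the 100 retested patients is not given. The interval from 0.60 to 1.00 is therefore an illustration.

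Fourth, it is tempting to set the kappa widths against the printed 0.12 and report a ratio of 2.0 to 3.3 (0.235/0.12 to 0.400/0.12). Part of that ratio comes from the printed limits being 90% limits, so the fair comparator is 0.145.

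Fifth, a reader might think nurse-GP agreement is also held to 100 pairs. The article applies 100 to test-retest alone.

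What the reply does not remove is that the article states both the sizing statistic and the analysis statistics, and the printed figures, labelled 95%, do not describe those that will be reported. This is stated text, not detail left to an analysis plan.

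**Conclusion.** The point holds in a limited form. The precision printed for n = 100 is a 90% Pearson precision labelled 95%. Taken as a pair, the limits are not the 95% precision of the ICC or of an unweighted dichotomous kappa. For the ICC the correction is small: at 0.80 the lower limit falls from 0.73 to 0.72 and the width rises from 0.12 to 0.144, and n = 100 remains a sensible basis. For kappa the article is silent. Under the assumptions above, the lower limit at 0.80 lies between 0.60 and 0.68, for positive rates of 10% to 50%.

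The ICC result needs only two administrations per patient. The kappa result rests on the unweighted two-category form and on the assumed positive rates. The matter touches the third aim, the psychometrics of the GPCOG. The primary outcomes and the main sample size do not depend on it, so it is minor.

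**What to change.** In *Sample size*, replace the two Pearson intervals with 95% ICC intervals as the basis for n = 100: about 0.855 to 0.932 at 0.90, and about 0.72 to 0.86 at 0.80. Add one sentence that states the form of kappa (weighting and cut-off), an assumed GPCOG-positive rate and the interval expected under it. For an unweighted dichotomous kappa of 0.80 that would be about 0.65 to 0.95 at 20% positive. In *Test parameters of the GPCOG*, describe test-retest kappa as supportive of the ICC.

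Nurse-GP reliability needs no change, since it can use every available pair.

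The cost is wording only, with no added patients or assessments. The one drawback is that the stated precision becomes slightly less favourable.

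### The 95% confidence intervals given for GPCOG test-retest reliability at n = 100 are slightly too narrow, clearly so at a correlation of 0.80

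*Protocol article*

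**What the plan says.** The last paragraph of the Sample size section plans the reliability sample separately from the main calculation: "For an estimate of test re-test reliability on the GPCOG a sample size of 100 will be used". The reason given is precision, not power: "to ensure the correlation is estimated to a reasonable precision". Two intervals then show what that precision would be: "The 95% confidence interval for a Pearson correlation of 0.9 would be [0.86, 0.93] and for a correlation of 0.80 [0.73, 0.85". The paragraph gives no other sample size, confidence level or sidedness, and no target width or lower bound for the reliability estimate. Test-retest reliability of the GPCOG belongs to the third aim in the Aims of the study section.

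**The concern.** The two intervals are the only figures offered in support of 100 patients for this estimate. Everything needed to check them is in the same paragraph: the correlation, the number of patients and the confidence level. At a correlation of 0.80 both printed limits look too close to the estimate for a 95% interval with 100 pairs. If so, the label, the limits and the sample size cannot all be right, and a reader is promised somewhat more precision than the sample gives. This is a misstatement in the text, so a fuller protocol or an analysis plan would not resolve it by adding detail.

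**Working it through.** **Inputs**, all from the Sample size section: n = 100; r = 0.9 with printed limits 0.86 and 0.93; r = 0.80 with printed limits 0.73 and 0.85; stated confidence 95%, taken as two-sided.

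**Formula.** Fisher z interval: tanh(atanh(r) ± q / √(n − 3)), with q = 1.96 for 95% and q = 1.645 for 90%.

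**Common quantities.** The standard error is 1/√97 = 0.1015; atanh(0.9) = 1.4722; atanh(0.80) = 1.0986. The half-width on the z scale is 1.96 × 0.1015 = 0.199 at 95% and 1.645 × 0.1015 = 0.167 at 90%.

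**Reproducing the printed figures.** At 95% they are not reproduced. At 90% all four are.

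| r | Printed as 95% | Fisher z, 95% | Fisher z, 90% |
|---|---|---|---|
| 0.9 | 0.86 to 0.93 | 0.8547 to 0.9317 | 0.8631 to 0.9274 |
| 0.80 | 0.73 to 0.85 | 0.7161 to 0.8611 | 0.7313 to 0.8526 |

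To two decimals the 95% intervals are [0.85, 0.93] and [0.72, 0.86], so three of the four printed limits differ.

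**Size at r = 0.80.** The 95% width is 0.8611 − 0.7161 = 0.145, against 0.85 − 0.73 = 0.12 as printed. The lower limit is off by 0.73 − 0.7161 = 0.014 and the upper by 0.8611 − 0.85 = 0.011. Rounding does not explain this: limits that round to 0.73 and 0.85 must lie between 0.725 and 0.855, and the 95% limits fall outside that range at both ends.

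**Size at r = 0.9.** The upper limit is 0.93 at either confidence level. The 95% lower limit, 0.8547, misses rounding up to 0.86 by only 0.855 − 0.8547 = 0.0003. This interval alone would be weak evidence of an error.

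**Does another 95% method give the printed interval at r = 0.80, n = 100?**

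| Method | 95% interval |
|---|---|
| Exact, from the sampling density of r | 0.714 to 0.860 |
| Fisher z with t quantile | 0.715 to 0.862 |
| Bias-corrected Fisher z | 0.714 to 0.860 |
| Hotelling z | 0.712 to 0.858 |
| Wald, standard error (1 − r²)/√(n − 1) | 0.729 to 0.871 |
| Wald, standard error √((1 − r²)/(n − 2)) | 0.681 to 0.919 |
| One-way intraclass correlation, two measurements | 0.717 to 0.861 |

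None does. The first Wald form matches the lower limit but not the upper.

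**Which confidence levels fit n = 100?** For r = 0.80, levels of about 88.3% to 91.6% round to the printed limits. For r = 0.9, levels of about 88.4% to 94.8% do. The common range, about 88.4% to 91.6%, contains 90% and excludes 95%.

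**The case against.** The strongest objection is that nothing depends on the difference. The protocol sets no required width, lower bound or test for the reliability estimate. It asks only for reasonable precision, and [0.72, 0.86] can be called as reasonable as [0.73, 0.85]. The interval finally reported will be calculated from the data, so the planning slip does not carry forward. All of this stands. It limits the importance of the point but does not make the printed limits correct.

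Four stronger readings are tempting, and the document does not support them.

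- A reader might infer that the authors certainly used 90% intervals. The match is exact, but true 95% intervals for any n from 128 to 154 round to the same four limits. That alternative contradicts the stated n = 100, so the text is inconsistent on either reading, but the source of the slip is not documented.
- A reader might infer that the reliability sample is too small and that 128 patients are needed. That figure is only the smallest n at which the 95% limits round to the printed ones. The protocol never made those limits a target, so there is no shortfall.
- A reader might object that precision is planned for a Pearson correlation, while the section on test parameters of the GPCOG says that reliability "will be calculated, using the kappa coefficient and intra-class correlation coefficient". For the intraclass coefficient this makes practically no difference: the one-way 95% interval is 0.717 to 0.861 at 0.80, against 0.716 to 0.861 by Fisher z. That section also covers reliability between nurse and GP, and does not say which coefficient serves the test-retest comparison.
- A reader might count the interval at 0.9 as an equal error. It is not. The one-way intraclass interval there, 0.8551 to 0.9315, even rounds to the printed [0.86, 0.93].

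**Conclusion.** The point holds as a minor arithmetic error. At n = 100 the printed 95% interval for a correlation of 0.80 is too narrow at both ends, by about 0.01 per limit, and this interval decides the matter. The one for 0.9 differs only in the last digit of its lower limit. The conclusion assumes a two-sided interval and the stated n = 100. At 0.80 it does not depend on the choice among the interval methods tried. It does not depend either on whether the slip lies in the multiplier or in the sample size used for the calculation.

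The consequence is confined to the reliability part of the third aim. The primary outcomes, the 168 patients with dementia and the 2,000 participants overall rest on separate calculations and are unaffected. Nothing here shows that 100 patients are inadequate for estimating reliability.

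**What to change.** In the last paragraph of the Sample size section, do one of two things. Either keep the 95% label and print [0.85, 0.93] for 0.9 and [0.72, 0.86] for 0.80, or keep the printed limits and relabel them as 90% intervals. The first is preferable if 95% is the level intended for reporting. Naming the Fisher z method in the same sentence would let a reader reproduce the figures. Keep n = 100. The cost is three changed digits or one changed confidence level, with no effect on recruitment, data collection or analysis.

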### Study drop outs/withdrawals

#### Subjects

We aim to recruit 2000 subjects, based on a dementia prevalence rate of 10% in the Australian population aged 75 years and over [37]. We anticipate a 10% drop out per annum, giving us 180 subjects with dementia at the 12 month mark, and 162 at 24 months, with a small number of incident cases.

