**Methods:**

The study is a cluster randomised trial, conducted across three states and five sites. All GPs will complete an audit of their consenting patients aged 75 years or more at three time points - baseline, 12 and 24 months. GPs allocated to the intervention group will receive two educational sessions from a peer GP or nurse, and will administer the GPCOG to consenting patients at baseline and 12 months. The first education session will provide information about dementia and the second will provide individualised feedback on audit results. GPs in the waitlist group will receive the RACGP Guidelines by post following the 12 month audit

Outcomes: Primary outcomes are carer and consumer quality of life and depression. Secondary outcomes include: rates of GP identification of dementia compared to a more detailed gold standard assessment conducted in the patient's home; GP identification of differential diagnoses including reversible causes of cognitive impairment; and GP referral to specialists, Alzheimers' Australia and support services. A "case finding" and a "screening" group will be compared and the psychometrics of the GPCOG will be examined.

Sample size: Approximately 2,000 subjects aged 75 years and over will be recruited through approximately 160 GPs, to yield approximately 200 subjects with dementia (reducing to 168 by 24 months).

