### Patients and support persons

Patients will be recruited by a mail out from each consenting GP to all eligible patients on their database. Patient participants will return their consent in reply paid envelopes to the study centre. Patients will be interviewed by study personnel blind to the group allocation of the patient and their GP. For patients scoring in the dementia range on the CAMCOG instrument (described below), the interviewer will request that they nominate a support person, if available, to take part in the study. Nominated support people will be given a consent form and information sheet for recruitment into the study.

Inclusion criteria for patients:

• Aged 75 years or over

• Listed on participating GPs' databases

• Visited recruited GPs within the last 24 months

• Consent to a home visit or surgery visit by project staff

• Speak and understand English

Inclusion criteria for support persons:

• Identified as a carer or support person by a patient scoring in dementia range on CAMCOG instrument

• Prior consent from the person with dementia for his/her carer to participate in the study

• Speak and understand English

• Consent to a home visit or surgery visit by the project staff.

Exclusion criteria for patients:

• Parkinson's disease, multiple sclerosis, motor neuron disease or central nervous system inflammation

• Psychotic symptoms prior to recruitment

• Developmental disability

• Insufficient English to complete a psychometric assessment (judged by interviewer)

• Progressive malignancy

• Substance abuse

• Deemed too sick to complete study by the GP

• Lives in a residential aged care facility at entry to the study

• Does not meet inclusion criteria

• Valid and informed consent cannot be obtained from the person involved and they do not have a person responsible for them.

Exclusion criteria for support persons:

• Insufficient English to complete testing (judged by the interviewer)

• Non-consenting patient-participant

• Does not consent to a home visit or surgery visit by the project staff.

• Too unwell to participate

• De not meet inclusion criteria.

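### The expected dementia counts of 200, 180 and 162 apply an all-population prevalence of 10% to a selected community sample, so they are unsupported and probably optimistic.

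*Protocol article*

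**What the plan says.** The Sample size section of the protocol article asks for 54 dementia patients per group after allowing for clustering. It then plans 56 in the waitlist arm and 112 in the intervention arm, 168 in all. The larger intervention arm is there so that case-finding and screening patients, assumed to be about half each, can be compared within it.

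The total follows from a prevalence: "Based on a dementia prevalence of approximately 10% in over 75 year old Australians [37], we aim to recruit a total of 2,000 participants". The Subjects paragraph under Study drop outs/withdrawals ties the figure to the same population, "We aim to recruit 2000 subjects, based on a dementia prevalence rate of 10% in the Australian population aged 75 years and over", and continues: "We anticipate a 10% drop out per annum, giving us 180 subjects with dementia at the 12 month mark, and 162 at 24 months". It also expects a few incident cases, without a number. The abstract speaks of recruiting enough people "to yield approximately 200 subjects with dementia (reducing to 168 by 24 months").

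The patient exclusion criteria, under Patients and support persons, include: "Lives in a residential aged care facility at entry to the study". They also remove people the GP considers too ill, people with Parkinson's disease and certain other neurological conditions, people with earlier psychotic symptoms, and people from whom valid consent cannot be had and who have no responsible person. Entry is by mailed invitation and returned consent. The practice criteria likewise refer to patients who live in the community.

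**The concern.** The 10% belongs to everyone aged 75 or over, whereas the sample is drawn from those who live in the community, are well enough and return a consent form. The Background itself notes that people with dementia live either at home or in residential care. If 10% is right for the whole population, removing any group with a prevalence above 10% leaves a remainder below 10%. It is reasonable to assume that aged-care residents are such a group, although the article gives no figure for them.

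Power is calculated on dementia patients, while the headline target is 2,000 people. The Discussion paragraph of the abstract reports 2,034 recruited and no dementia count. The headline target can therefore be met without anyone knowing whether the number that carries the power has been reached.

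**Working it through.** **Inputs from the article.** Total 2,000; prevalence 10%; loss 10% a year; allocation 2:1; 54 per group required at 90% power and type 1 error 0.05; 56 and 112 planned; intervention arm split about 50:50 into case finding and screening; patient and carer outcomes compared at 12 months (Statistical analyses, the question on better health outcomes).

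**Reproducing the plan.** Yield = N × prevalence × 0.9^years.
- Baseline: 2,000 × 0.10 = 200
- 12 months: 200 × 0.9 = 180
- 24 months: 200 × 0.81 = 162

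All three match, so the 10% was used unadjusted. (The abstract's 168 at 24 months does not follow from these inputs.)

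**Break-even for the planned 168.**
- If 168 is meant at baseline: 168 / 2,000 = 8.4%
- At 12 months: 168 / 1,800 = 9.33%
- At 24 months: 168 / 1,620 = 10.37%, so the plan is six short there even at 10%, before incident cases

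**Break-even for waitlist versus intervention, on the plan's premise.** With 54 v 54, the variance factor is 2/54 = 0.0370. At 2:1 with n in the waitlist arm it is 1/n + 1/(2n) = 1.5/n. Equating the two gives n = 40.5, or about 41 v 82 and about 122 in all. At 12 months: 122 / 1,800 = 6.8%.

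**Break-even for case finding versus screening.** The intervention arm at 12 months holds 2/3 × 1,800 × p = 1,200p dementia patients.
- For the planned 112: 112 / 1,200 = 9.33%
- For 54 per half (108): 108 / 1,200 = 9.0%

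**Yield over a range of eligible prevalence.**

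| Prevalence | Cases at 0 / 12 / 24 months | Waitlist / intervention at 12 months | Each half of intervention arm at 12 months |
|---|---|---|---|
| 10% | 200 / 180 / 162 | 60 / 120 | 60 |
| 9% | 180 / 162 / 146 | 54 / 108 | 54 |
| 8% | 160 / 144 / 130 | 48 / 96 | 48 |
| 7% | 140 / 126 / 113 | 42 / 84 | 42 |
| 6% | 120 / 108 / 97 | 36 / 72 | 36 |

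**Approximate 12-month power if 54 per group gives 90%.** Power = Φ(3.24 × √(variance factor at 54 v 54 ÷ actual variance factor) − 1.96), where 3.24 = 1.96 + 1.28.
- Waitlist v intervention stays above 90% down to 7%. At 6% the factor is 1.5/36 = 0.0417, the root is √(0.0370/0.0417) = 0.943, and power is about 86%.
- Case finding v screening: at 8%, √(48/54) = 0.943 gives about 86%; at 7%, √(42/54) = 0.882 gives about 82%; at 6%, √(36/54) = 0.816 gives about 75%.

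**How far could eligible prevalence fall?** Eligible prevalence = (g − r × q)/(1 − r), where g is all-population prevalence, r the share of people aged 75+ in residential care and q the prevalence among residents. The article gives neither r nor q. With g = 10% and assumed r = 5–10% and q = 30–70%, the result runs from (0.10 − 0.07)/0.90 = 3.3% to (0.10 − 0.015)/0.95 = 8.9%, or about 67 to 179 baseline cases. With g = 12%, r = 5%, q = 50% it is 0.095/0.95 = 10.0%, or 200 cases. With g = 13%, r = 8%, q = 50% it is 0.09/0.92 = 9.8%, or 196 cases.

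**The case against.** A reader might infer that 2,000 participants cannot deliver the yield and that the primary comparison will be well short. The documents do not support either statement.

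- **No prevalence is given for the eligible or the excluded groups.** The range above is only as good as its assumed shares. That the exclusions other than aged care remove dementia disproportionately is plausible but not stated. The consent exclusion applies only where there is also no responsible person.
- **The 10% may itself be low.** The Background puts prevalence at about 1 in 5 over age 80. If half of those aged 75+ are over 80 (an assumption), the whole group reaches 10% with no younger cases at all. Requiring a GP visit within 24 months could enrich the sample, and the CAMCOG dementia range need not match the definition behind the cited 10%.
- **The 56 and 112 are not what waitlist versus intervention needs.** The requirement is 54 per group, and the intervention arm was doubled for the case-finding question. About 41 v 82 carries the same precision.
- **The target is already stated as 168 dementia patients,** and recruitment has passed 2,000, so the assumption no longer steers it.

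These arguments limit the size of the problem and protect the waitlist v intervention comparison over much of the range. They do not supply the missing adjustment: the article relies on 10% and invokes none of these offsets. Nor do they protect the case-finding comparison, where the slack is small.

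**Conclusion.** The mismatch of populations holds. The 200/180/162 counts describe all Australians aged 75 or over, not the people the criteria admit, and they are probably optimistic. The amount cannot be determined from the documents.

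At 12 months the planned 168 is missed below about 9.3% eligible prevalence. The consequence falls mainly on case finding versus screening, which drops under 54 per half below 9.0%. Waitlist versus intervention is affected only below about 6.8%.

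These thresholds take as given the plan's 54 per group, its 10% yearly loss, exact 2:1 and 50:50 splits, and no incident cases. The case-finding figures also carry over the between-practice clustering allowance, although that comparison lies largely within practices. Whether 54 is itself correctly derived is a separate question.

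**What to change.** 1. In Sample size and in Subjects, replace the all-population 10% with a justified prevalence for the eligible, community-living, consenting population, or show the yield over a range such as the 6% to 10% table above. Restate the 200, 180 and 162 to match.
2. Report the count of baseline CAMCOG-dementia patients, pooled over arms and blinded to allocation, and restate power or the detectable difference at that count for both waitlist v intervention and case finding v screening.
3. Judge recruitment by the 168 dementia patients rather than by 2,000 enrolled, and say at which time point the 168 is meant to hold.

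The cost is one query of data already collected and revised text; the design and analysis do not change. The drawback is that the stated yield and power may look less favourable.
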